## Abstract

**Background:**

Postoperative pulmonary complications (PPCs) are major causes of morbidity, mortality, and prolonged hospital stay in patients after surgery. Using effective strategies to prevent its occurrence is essential to improve outcome. However, despite various efforts, the incidence of PPCs remains elevated in high-risk patients. Anticholinergic inhalation is used to reduce high airway resistance and improve pulmonary function; it may be helpful to decrease the risk of PPCs. Penehyclidine is a long-acting anticholinergic agent which selectively blocks M1 and M3 receptors. We hypothesize that, in high-risk patients, prophylactic penehyclidine inhalation may decrease the incidence of PPCs.

**Methods:**

This is a randomized, double-blind, placebo-controlled trial with two parallel arms. A total of 864 patients at high risk of PPCs will be enrolled and randomized to receive prophylactic inhalation of either penehyclidine or placebo (water for injection). Study drug inhalation will be administered from the night (7 pm) before surgery until the second day after surgery, in an interval of every 12 hours. The primary outcome is the incidence of PPCs within 30 days after surgery. Secondary outcomes include the time to onset of PPCs (from end of surgery to first diagnosis of PPCs), the number of PPCs (indicates the number of diagnosed individual PPCs), the incidence of postoperative extrapulmonary complications, the length of stay in hospital after surgery, and the 30-day all-cause mortality.

**Discussion:**

Results of the present study will provide evidence to guide clinical practice in using prophylactic inhalation of an anticholinergic to prevent PPCs in high-risk patients.

**Trial registration:**

The study was registered prospectively in Chinese Clinical Trial Registry (www.chictr.org.cn, ChiCTR-IPC-15006603) on 14 May 2015 and retrospectively in ClinicalTrials.gov (NCT02644876) on 30 December 2015.

**Electronic supplementary material:**

The online version of this article (doi:10.1186/s13063-017-2315-7) contains supplementary material, which is available to authorized users.

## Background

Postoperative pulmonary complications (PPCs) are major causes of morbidity, mortality, and prolonged hospital stay in patients after surgery [1, 2]. The reported incidences of PPCs vary from 5% to 70% depending on the definition of PPCs, the type of surgical procedures, and the population of patients included in the study [1]. The ARISCAT study identified seven independent predictors, including four patient-related factors and three surgery-related factors, and built a predictive model for the risk of PPCs [3]. A subsequent study confirmed that, in high-risk patients (i.e., patients with cumulative ARISCAT risk score ≥ 45), the incidence of PPCs was as high as 38% (25–51%) [4].

Changes in pulmonary physiology after major thoracic or upper abdominal surgery include diaphragmatic dysfunction, reduced vital capacity, postoperative pain and splinting, and impaired clearance of airway secretions [5]. Affected patients are at increased risk to develop atelectasis, pneumonia, and other respiratory complications. Prophylactic inhalation of anticholinergic agents may be helpful in preventing PPCs by dilating bronchus, decreasing mucous secretion and relieving airway hyperresponsiveness (AHR). In a retrospective study of patients with COPD requiring lung cancer surgery, perioperative inhalation of tiotropium was associated with decreased cardiopulmonary complications after surgery [6]. In a randomized controlled trial of gastric cancer patients with COPD, perioperative (1 week before and 2 weeks after surgery) inhalation of tiotropium decreased the incidence of postoperative complications in those with moderate COPD [7].

Theoretically, selective M1 and M3 receptors blockers may have advantages over nonselective blockers (such as tiotropium bromide) for the purpose of bronchodilation [8]. Penehyclidine is a long-acting anticholinergic agent which selectively blocks M1 and M3 receptors [9, 10]. In a pilot randomized controlled trial of our group, 90 elderly (≥65 years) patients who were admitted to the ICU after long-duration (≥3 hours) surgery randomly received inhalation of penehyclidine, ipratropium bromide, or normal saline for 3 consecutive days. The results showed that prophylactic anticholinergic inhalation significantly reduced the incidence of postoperative bronchospasm (1/30 [3.3%] with penehyclidine hydrochloride, 1/31 [3.2%] with ipratropium bromide, and 6/29 [20.7%] with normal saline, respectively, *P* = 0.025) [11]. We hypothesize that, in high-risk patients, prophylactic inhalation of penehyclidine may decrease the incidence of PPCs.

The purpose of this study is to investigate the impact of prophylactic penehyclidine inhalation on the incidence of PPCs in high-risk patients after major surgery.

## Methods/Design

### Study design

This registered prospective, single-center, randomized, double-blind, placebo-controlled trial with two parallel arms is to test the superiority of the intervention. Eligible patients will be enrolled and randomly assigned to receive one of two interventions, i.e., penehyclidine hydrochloride inhalation or placebo (water for injection) inhalation (Fig. 1). The study will be coordinated and conducted in the Department of Anesthesiology and Critical Care Medicine of Peking University First Hospital, a tertiary academic hospital in Beijing. The protocol is reported according to the Standard Protocol Items: recommendations for randomized controlled trials (Fig. 2 SPIRIT diagram and Additional file 1 SPIRIT checklist).

**Fig. 1 Fig1:**
[figure not shown]
Flowchart of the study

**Fig. 2 Fig2:**
[figure not shown]
SPIRIT diagram

### Participants

The inclusion criteria are (1) patients of 50 years or over, (2) scheduled to undergo upper abdominal or noncardiac thoracic surgery with expected duration of 2 hours or longer. For those who undergo thoracoscopic or laparoscopic surgery, the expected length of incision must be 5 cm or more, and (3) judged to be at high risk of PPCs according to the ARISCAT risk score (cumulative ARISCAT risk score ≥ 45, see Table 1).

**Table 1 Tab1:** ARISCAT (Canet) risk index

Independent predictors of risk for PPCs		Risk score
Age, years		
≤ 50		0
51–80		3
> 80		16
Preoperative SpO_2_, %		
≥ 96%		0
91–95%		8
≤ 90%		24
Respiratory infection in the last month		
No		0
Yes		17
Preoperative anemia (HbO_2_ ≤ 10 g/dl)		
No		0
Yes		11
Surgical incision		
Peripheral		0
Upper abdominal		15
Intrathoracic		24
Duration of surgery, hours		
≤ 2		0
2–3		16
> 3		23
Emergency procedure		
No		0
Yes		8
Risk class	Number of points in risk score	Pulmonary complications rates
Low risk	<26 points	1.6%
Intermediate risk	26–44 points	13.3%
High risk	≥45 points	42.1%

*PPC* postoperative pulmonary complications

Patients who meet any of the following criteria will be excluded: (1) American Society of Anesthesiologists (ASA) physical classification ≥ IV or the expected survival duration ≤ 24 hours; (2) preoperative history of moderate-to-severe symptomatic prostatic hypertrophy or narrow-angle glaucoma; (3) history of myocardial infarction, severe heart dysfunction (New York Heart Association functional classification ≥ 3) or tachyarrhythmia within 1 year; (4) inhalation of β2-receptor activator, M-receptor blockers and/or glucocorticoids within 1 month before surgery; (5) severe renal dysfunction (requirement of renal replacement therapy) or severe hepatic dysfunction (Child-Pugh grade C); (6) history of acute stroke within 3 months before surgery; (7) unable to cooperate in the inhalational therapy; (8) participation in other clinical trial during the last month or within the six half-life periods of the study drug used in the last trial; or (9) refuse to participate in the study.

Criteria of dropout include the following: (1) consent withdrawn by the participants themselves (at least one dose of study drug has been administered); (2) loss to follow‐up; (3) ordered to exit by the investigators or attending physicians (poor compliance, occurrence of severe complications, or occurrence of severe adverse events); (4) prophylactic use of any prohibited drugs (anticholinergics or any medications other than the study drugs) from study recruitment to postoperative day 2; or (5) blindness unmasked. For dropout cases, detailed reasons will be recorded in the case report forms (CRFs). The primary therapeutic effects recorded the last time will be regarded as the final results. These cases will be included in the intention-to-treat analysis but excluded from the per protocol analysis.

Criteria of rejection include the following: (1) consent withdrawn by the participants themselves (study drug is not administered); (2) no study record; or (3) surgery delayed or canceled, unable to assess the occurrence of PPCs. For rejected cases, detailed reasons will be recorded in the CRFs. These cases will be excluded from analysis of therapeutic effects.

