### Randomized, blinding and study drug administration

Random numbers were generated in a 1:1 ratio using the SAS 9.2 software package (SAS Institute, Cary, NC, USA) by a biostatistician. Randomization will be stratified according to the type of surgery (upper abdominal or noncardiac thoracic surgery). Study drugs (penehyclidine hydrochloride 1 mg/1 ml, or water for injection 1 ml) are provided as clear aqueous solution in the same 1 ml ampoules (manufactured by Chengdu List Pharmaceutical Co., Ltd., Sichuan, China) and labeled according to the randomization results by a biostatistician and a pharmacist who are independent of patient recruitment and data collection. The results of randomization are sealed in the envelopes and stored at the site of investigation until the end of the study.

During the study period, consecutively recruited patients will be assigned sequential numbers according to which the study drugs will be dispensed by a study coordinator. Study drugs are administered by inhalation in the night (7 pm) before surgery, in the morning (7 am) of surgery, and then every 12 hours until postoperative day 2, resulting in a total number of 7 inhalations. Study drug inhalation is performed with a jet nebulizer (DNA100, manufactured by Congren Medical Equipment Co., Ltd., Xiamen, China) for extubated patients or a vibrating mash nebulizer (Agrogen Professional Nebulizer System, AG-AP6000CH, Aerogen Ltd, Ireland) for patients with mechanical ventilation. Before inhalation, study drugs (penehyclidine hydrochloride 0.5 mg/0.5 ml for patients in the penehyclidine group, or water for injection 0.5 ml for patients in the placebo group) are diluted with normal saline to 6 ml. The performance of each study drug inhalation is recorded in the CRFs.

Patients, investigators, and healthcare team members are all blinded to the study group assignment throughout the study period. In case of an emergency (such as development of a severe adverse event), attending physicians or surgeons can request unmasking of the treatment allocation. These situations will be documented; but analyses will be performed on the intention-to-treat population.

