### Anesthesia and perioperative management

Intraoperative monitoring include electrocardiogram, pulse oxygen saturation, noninvasive blood pressure, airway pressure, end-tidal carbon dioxide concentration, nasopharyngeal temperature, urine output, and bispectral index (BIS) value. Intra-arterial pressure (and derivative parameters such as stroke volume variation by FloTrac system) and central venous pressure are monitored when considered necessary.

Anesthetic premedication is not administered. Prophylactic antibiotics (the first or second generation cephalosporin, with or without metronidazole, or cephamycins) are administered 30 minutes to 1 hour before surgical incision. The duration of prophylactic antibiotic treatment is less than 48 hours. The choice of antibiotics and the duration of prophylactic antibiotic therapy are decided according to the *Guiding Principles of Clinical Use of Antibiotics* (published by Chinese National Health and Family Planning Commission in 2015) http://www.nhfpc.gov.cn/zwgkzt/wsbysj/200804/18544.shtml. Therapeutic antibiotic agents are only indicated in patients who are diagnosed with infection.

General anesthesia with endotracheal intubation is performed for all patients. Anesthesia is induced with intravenous propofol or etomidate, sufentanil, and rocuronium, or cisatracurium, and maintained with intravenous propofol, remifentanil and/or sufentanil, and rocuronium or cisatracurium, with or without inhalational sevoflurane and/or nitrous oxide. Neuraxial block is performed depending on the decision of attending anesthesiologists. BIS value is maintained between 40 and 60. Mechanical ventilation is established with a tidal volume from 6 to 8 ml/kg, a positive end-expiratory pressure from 0 to 5 cm H2O, a frequency from 12 to 16 breaths per minute, and 50% oxygen (mixed with nitrous oxide or air). Higher oxygen concentration is administered during one-lung ventilation. Fluid management is performed according to routine practice. Packed red blood cells are transfused to maintain a hemoglobin level above 7 g/dl. Anticholinergics are prohibited unless being used for the treatment of bradycardia, in which case atropine is administered.

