At the end of surgery, patients are transferred to the postoperative care unit (PACU) after extubation and monitored for at least 30 minutes before being sent back to the general wards. For patients who are transferred to the intensive care unit (ICU) with endotracheal intubation, propofol and/or dexmedetomidine sedation are provided in addition to opioid analgesia; mechanical ventilation is performed with bilevel ventilation mode (established with a low level at 3 to 5 cm H_2_O, a high level between 13 and 16 cm H_2_O, and a trigger flow at 2 to 3 l/min; PB 840 ventilator, Puritan-Bennett Corp., Mervue, Ireland). Patients are extubated as soon as they meet the criteria of extubation (regain consciousness and airway protective reflex, normal circulatory status and temperature, no residual neuromuscular blockade). For patients requiring mechanical ventilation of more than 24 hours, a ventilator weaning protocol is executed in order to extubate patients as soon as possible (Additional file 2). For patients with acute respiratory failure, noninvasive positive pressure ventilation is used to promote early extubation or to avoid reintubation. For all patients after extubation, low-flow supplemental oxygen is routinely provided during the day of surgery.

During the postoperative period, patient-controlled analgesia (either intravenous or epidural) is provided for up to 3 days after surgery. The target is to maintain a Numeric Pain Rating Scale (NPRS, an 11-point scale where 0 = no pain and 10 = the worst pain) pain score of 3 or less. Nonsteroidal anti-inflammatory drugs are administered when considered necessary and without contraindications. Other treatments including chest physiotherapy, early mobilization, removal of nasogastric tube, parenteral or enteral nutrition, and intravenous respiratory medications (such as expectorants, theoclears and glucocorticoids) are administered according to routine practice.

During the study period, inhalations of any respiratory medications for prophylactic purpose other than the study drugs are prohibited. However, for patients who develop PPCs, inhalation of respiratory medications is allowed. For those who develop harmful effects or clinical deterioration, the dose of study drugs can be decreased or the study drug administration can be discontinued on request of participants, attending surgeons or investigators. These situations will be recorded in the CRFs.

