### Data analysis

#### General principles

All statistical analyses will be performed with SPSS 14.0 software package (SPSS, Chicago, IL, USA) and SAS 9.2 software (SAS Institute, Cary, NC, USA) by statisticians in the Department of Biostatistics of Peking University First Hospital. Since the safety of intervention has been confirmed by our previous pilot study, interim analysis is not planned. Analyses will be performed on an intention-to-treat basis, that all subjects will be analyzed in the group which they were assigned to. For the primary outcome (the incidence of PPCs within 30 days after surgery), per protocol analysis will also be performed.

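### The per-protocol analysis of PPCs can exclude some patients because they had the primary outcome; intention-to-treat is not affected by this exclusion

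*Protocol article*

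**What the plan says.** The relevant rules are spread over several sections of the protocol article.

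- **Participants, dropout criteria.** Criterion 3 covers patients "ordered to exit by the investigators or attending physicians (poor compliance, occurrence of severe complications, or occurrence of severe adverse events". Criterion 4 covers "prophylactic use of any prohibited drugs (anticholinergics or any medications other than the study drugs) from study recruitment to postoperative day 2". Criterion 5 is unmasking.
- **Participants, handling of dropouts.** "These cases will be included in the intention-to-treat analysis but excluded from the per protocol analysis". For the outcome value, "The primary therapeutic effects recorded the last time will be regarded as the final results".
- **Randomized, blinding and study drug administration.** "In case of an emergency (such as development of a severe adverse event), attending physicians or surgeons can request unmasking of the treatment allocation". The section adds that analyses stay on the intention-to-treat population. It does not return such patients to the per-protocol set.
- **General principles.** Intention-to-treat is the basis of analysis. For the primary outcome, "per protocol analysis will also be performed".
- **Primary outcome and Adverse events.** The endpoint counts PPCs of Clavien-Dindo grade II or above within 30 days, including respiratory failure and respiratory infection. A severe adverse event is defined by consequences such as death, threat to life or a longer stay. PPCs are not set apart from it.

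**The concern.** A per-protocol set is normally restricted by what treatment the patient received and whether the patient was eligible. Here one ground for exclusion is a clinical event that may itself be the endpoint. After thoracic or upper abdominal surgery, a serious respiratory failure or pneumonia fits both severe complication and severe adverse event. If it leads to an ordered exit, or to unmasking, the patient and the endpoint event both leave the analysis of that endpoint.

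What is at stake is how far this analysis can support the main result. Agreement or disagreement with intention-to-treat could partly reflect who was ordered out and not the effect of the drug in adherent patients.

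**Working it through.** **Inputs from Sample size calculation.** Placebo PPC rate 42.1%; reduction of 10 points, so 32.1% on penehyclidine; one-sided 0.025; 80% power; 360 per group, 432 enrolled per group.

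**The plan's own figure.** With p1 = 0.421, p2 = 0.321 and mean 0.371:

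- Pooled formula: n = [1.960·√(2·0.371·0.629) + 0.842·√(0.421·0.579 + 0.321·0.679)]² / 0.10² = 366 per group.
- Unpooled formula: 363 per group.
- Power at 360 per group: 79.4%.

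The stated 360 is therefore reproduced closely, and the 10% is an absolute reduction. These rates serve below as the true rates.

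**Effect of the exclusion.** Let p be the true PPC rate, f the share of PPC patients removed and g the share of patients without a PPC removed. The per-protocol rate is

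p(1−f) / [p(1−f) + (1−p)(1−g)].

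If only PPC patients are removed (g = 0), this becomes p(1−f)/(1−pf). The documents give neither f nor g, so every share below is an assumption.

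Example with f = 20%: placebo 0.421·0.8/(1−0.0842) = 0.3678; penehyclidine 0.321·0.8/(1−0.0642) = 0.2744; difference 0.0933.

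| True rates, placebo / drug | f, placebo / drug | Per-protocol rates | Difference, points |
|---|---|---|---|
| 42.1% / 32.1% | 0 / 0 | 42.1% / 32.1% | 10.0 |
| 42.1% / 32.1% | 5% / 5% | 40.9% / 31.0% | 9.9 |
| 42.1% / 32.1% | 20% / 20% | 36.8% / 27.4% | 9.3 |
| 42.1% / 32.1% | 30% / 30% | 33.7% / 24.9% | 8.9 |
| 42.1% / 32.1% | 10% / 20% | 39.6% / 27.4% | 12.1 |
| 42.1% / 32.1% | 20% / 10% | 36.8% / 29.8% | 6.9 |
| 42.1% / 42.1% | 10% / 20% | 39.6% / 36.8% | 2.8 |
| 42.1% / 42.1% | 20% / 10% | 36.8% / 39.6% | −2.8 |

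Differences are placebo minus drug, taken from unrounded rates. Equal removal lowers both rates but shifts the difference little. Unequal removal shifts it by about 2 to 3 points, in either direction.

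**Scale.** Equal removal of 20% means 432·0.421·0.2 = 36.4 placebo and 432·0.321·0.2 = 27.7 penehyclidine patients. Both fit within the 432 − 360 = 72 per group that the plan allows for dropout of every kind.

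**Limiting case.** If f = g, the formula returns p. Exits that are equally common with and without a PPC leave the rate at 42.1%.

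**Prohibited-drug wording.** No arithmetic applies; the texts are set side by side. Criterion 4 spells out prohibited prophylactic drugs as "prophylactic use of any prohibited drugs (anticholinergics or any medications other than the study drugs) from study recruitment to postoperative day 2". Anesthesia and perioperative management provides for "Prophylactic antibiotics (the first or second generation cephalosporin" and other agents before incision, and allows intravenous respiratory medications as routine. It states its ban as "inhalations of any respiratory medications for prophylactic purpose other than the study drugs are prohibited". The scope in Participants is wider than the scope in the management section.

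**The case against.** The strongest reply is that the main inference is safe. Intention-to-treat is the basis of analysis, keeps every dropout, and is restated for unmasked patients. This stands: the exclusion touches only a supportive analysis.

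Second, an event alone removes nobody; an exit order or unmasking must follow. The management section lets patients with PPCs receive inhaled respiratory drugs and allows the study drug to be reduced or stopped without calling this an exit. The follow-up section has deviators followed to the end. Severe complications can also be extrapulmonary. This stands too, and is why the selection is only partial. It does not remove the rule, because nothing bars a PPC from being the reason for exit.

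Third, blinding makes unequal removal less likely. True, but adverse effects of the drug can themselves prompt exits.

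Two stronger readings are tempting:

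- A reader might infer a large false benefit. Assuming 10% of placebo and 30% of penehyclidine PPC patients removed, with 42.1% true in both arms, gives 39.6% vs 33.7%, or 5.8 points. The documents support neither that threefold imbalance nor its direction.
- A reader might take criterion 4 literally and conclude that nearly every patient becomes a dropout because of prophylactic antibiotics. The criterion speaks of prohibited drugs, and the management section itself prescribes those antibiotics. The sensible reading is a loose parenthesis.

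**Conclusion.** The point holds as a defect in a stated rule. The per-protocol analysis of PPCs can lose patients because they had a PPC, by ordered exit or by unmasking after a severe adverse event, so it is partly selected on its own endpoint. The documents do not show that every severe PPC is lost, nor that the trial's main conclusion is biased.

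Size and direction cannot be determined from the documents. On the assumption that only PPC patients are removed, an equal 20% in both arms costs 0.7 points of a 10.0-point difference. A 10% vs 20% split under no effect produces 2.8 points for whichever arm loses more. Exits among patients without a PPC would reduce these shifts.

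The article names no other supporting analysis of the primary outcome. An analysis plan that is not shown may contain one, so this one should not be called the only check. The change is worth making because it is cheap, but it is not critical. The prohibited-drug wording is a separate, smaller inconsistency.

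**What to change.** 1. Define the per-protocol set by eligibility and adherence deviations that are judged under blind and not caused by the outcome. The exact adherence threshold can be left to the analysis plan.
2. Remove ordered exit for severe complications or severe adverse events, and unmasking that follows such an event, as reasons for exclusion from that set. These patients stay in with their PPC status counted.
3. State that this concerns membership of the analysis set only. The clinical rules on stopping treatment and on unmasking are unchanged.
4. Reconcile the prohibited-drug wording of the dropout criteria with Anesthesia and perioperative management, so that one scope applies throughout.

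The cost is wording in the protocol or analysis plan, before unblinding. No new data are needed: each inhalation and the reasons for dropout already go into the case report forms, and follow-up is already to be completed for patients who deviate from the intervention.

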### Patient follow-up and outcome assessment

Patients will be followed up twice daily until postoperative day 2, once daily from postoperative days 3 to 6, and then weekly until 30 days after surgery. Intraoperative data including type and duration of anesthesia, uses and doses of anesthetics, analgesics and other drugs, parameters of mechanical ventilation, fluid balance and transfusion of blood products, as well as type and duration of surgery will be collected. The final cumulative ARISCAT risk score will be calculated just after the surgery. Postoperative data including NRS pain scores, analgesic consumption, respiratory management, return of gastrointestinal function, start of nutrition, occurrence of complications and related treatment, admission to the ICU, duration of hospital stay, and any events that lead to return or readmission to hospital after hospital discharge will be recorded. Any adverse events or complications that occur during the study period will be promptly treated according to routine practice. For patients who deviate from the intervention protocol, deviations will be corrected when possible and follow-up will be completed. For patients who withdraw consent, the last follow-up results will be regarded as the final results.

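### Patients ordered out of the trial by staff have their last recorded primary result made final, although the follow-up section completes follow-up for protocol deviators; an exit before a PPC diagnosis can be scored as PPC-free

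*Protocol article*

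**What the plan says.** The Participants section of the protocol article lists five dropout criteria: (1) consent withdrawn after at least one dose; (2) loss to follow-up; (3) patients "ordered to exit by the investigators or attending physicians (poor compliance, occurrence of severe complications, or occurrence of severe adverse events"); (4) prophylactic use of prohibited drugs; (5) unmasking. The last two appear as "from study recruitment to postoperative day 2; or (5) blindness unmasked". Two sentences then apply to all five. The first sets the outcome value: "The primary therapeutic effects recorded the last time will be regarded as the final results". The second sets the analysis populations: "These cases will be included in the intention-to-treat analysis but excluded from the per protocol analysis".

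The section on patient follow-up and outcome assessment has twice-daily visits to postoperative day 2, then visits "once daily from postoperative days 3 to 6, and then weekly until 30 days after surgery". It continues: "For patients who deviate from the intervention protocol, deviations will be corrected when possible and follow-up will be completed". Its next sentence makes the last follow-up result final for patients who withdraw consent. No other group is named there.

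Three other sections bear on the point:

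- Anesthesia and perioperative management, on patients who are harmed or who worsen clinically: "the dose of study drugs can be decreased or the study drug administration can be discontinued on request of participants, attending surgeons or investigators".
- Randomization and blinding, on emergency unmasking: "These situations will be documented; but analyses will be performed on the intention-to-treat population".
- Adverse events: severe adverse events are monitored, followed up and recorded.

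The primary outcome is the incidence of PPCs of Clavien-Dindo grade II or above within 30 days, compared by a chi-squared test.

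**The concern.** The two sections give different instructions for overlapping patients. A poorly compliant patient is arguably a deviator whose follow-up is completed, yet if staff order that patient out, the last recorded result becomes final. For exits due to severe complications or severe adverse events, neither section clearly prevails.

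The outcome accumulates over 30 days, while study drug ends on postoperative day 2. An exit during dosing can therefore leave about four weeks unobserved, and carrying forward 'no PPC so far' turns an unknown outcome into a recorded non-event. Severe complications and severe adverse events are plausibly related to PPC risk, so such exits need not be random or equally frequent in the two groups. If exit ends observation, the number of PPCs, extrapulmonary complications, length of stay and 30-day mortality can be lost as well. A later analysis plan cannot recover outcomes that were never observed.

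**Working it through.** **1. Which rule applies to whom**

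| Patient | Participants section | Elsewhere in the protocol |
|---|---|---|
| Withdraws consent | last result final | last result final: agrees |
| Lost to follow-up | last result final | not addressed; no further data possible |
| Ordered out, poor compliance | last result final | arguably a deviator, follow-up completed: conflict |
| Ordered out, severe complication or severe adverse event | last result final | drug may be reduced or stopped and the event is followed; PPC assessment to day 30 not stated: unresolved |
| Prohibited drug | last result final | arguably a deviator, follow-up completed: conflict unless 'dropout' is only an analysis label |
| Unmasked | last result final | stays in intention-to-treat; need not end observation |

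**2. Effect on the primary outcome**

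A PPC diagnosed before exit, including one that prompts it, is already counted. Only PPCs arising after a PPC-free exit are lost.

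**3. Planning figures** (Sample size calculation)

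Inputs: 42.1% on placebo; a 10-point reduction, so 32.1% on penehyclidine; one-sided 0.025; 80% power; 360 per group, raised to 432 for about 20% dropout.

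A two-proportion formula without continuity correction gives 366 per group (pooled variance) or 363 (unpooled), within 3% of the stated 360. Power at 360 is 79.4%, and 360 × 1.2 = 432. The sample size is not in dispute.

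**4. Illustration**

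The rate of ordered exits is not given, so the shares below are assumptions. Let e be the share of a group that exits PPC-free. Assume these patients would later have had a PPC at their group's planning rate and that none of those PPCs is counted.

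- Observed rate = p(1 − e); uncounted PPCs = 432 × e × p.
- Power = Φ{[(p₁ − p₂) − 1.96·SE₀]/SE₁}, with SE₀ = √[2p̄(1 − p̄)/432] and SE₁ = √{[p₁(1 − p₁) + p₂(1 − p₂)]/432}, where p₁ and p₂ are the observed rates and p̄ is their mean.

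| Exits, placebo / penehyclidine | Uncounted PPCs | Observed rates | Difference | Power |
|---|---|---|---|---|
| none | 0 / 0 | 42.1% / 32.1% | 10.0 points | 86% |
| 1% / 1% | 1.8 / 1.4 | 41.7% / 31.8% | 9.9 | 86% |
| 5% / 5% | 9.1 / 6.9 | 40.0% / 30.5% | 9.5 | 83% |
| 10% / 10% | 18.2 / 13.9 | 37.9% / 28.9% | 9.0 | 80% |
| 5% / 2.5% | 9.1 / 3.5 | 40.0% / 31.3% | 8.7 | 76% |
| 2.5% / 5% | 4.5 / 6.9 | 41.0% / 30.5% | 10.6 | 90% |

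Worked row, 5% / 5%: 0.421 × 0.95 = 0.39995 and 0.321 × 0.95 = 0.30495, difference 0.0950. SE₀ = 0.03251 and SE₁ = 0.03234, so power = Φ[(0.0950 − 1.96 × 0.03251)/0.03234] = 0.833.

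As a rule of thumb, 1% of 432 is 4.3, so a net 4.3 missed PPCs in one group move its incidence by 1 point.

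**5. No true effect**

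With 42.1% in both groups, and assumed exits of 5% on placebo and 10% on penehyclidine:

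- All later PPCs missed: 40.0% v 37.9%, a spurious 2.1 points; one-sided rejection rises from 2.5% to 9.2%.
- Half missed: a spurious 1.1 points and 5.0% rejection.

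**The case against.** The strongest reply is that the sections can be reconciled. The Participants section says which value is used for a dropout; it does not say that observation stops. The follow-up section sends patients to day 30 without excepting those who exit, so the last record could be the day-30 record, and 'dropout' could merely mark exclusion from the per protocol set. Reducing or stopping drug, following up severe adverse events and keeping unmasked patients in the intention-to-treat population all point towards continued observation. The follow-up section also never says 'only' for withdrawn consent, the last-result sentence mentions primary effects alone, and a condensed article may leave detail to the full protocol.

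Part of this stands. The label reading suits prohibited drugs and unmasking. Loss of secondary outcomes is inferred from the word 'exit', not stated. The table in the working assumes that every later PPC is missed. If half are missed, the 5% / 2.5% case gives 0.421 × 0.975 − 0.321 × 0.9875 = 9.3 points and 82% power.

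The reconciliation is nonetheless stated nowhere. It would leave the last-result sentence nothing to do for ordered exits, and it sits badly with a criterion listed beside withdrawal and loss to follow-up. None of the supporting sections requires PPC assessment to day 30. Nor is this a matter of omitted detail: the article states a rule, and that rule sets the value of the primary outcome.

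**Conclusion.** The point holds. As written, a patient ordered out before a PPC is diagnosed can enter the intention-to-treat analysis as PPC-free, and the follow-up section does not clearly override this. The conflict is direct for poor compliance and unresolved for severe complications and severe adverse events.

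Size and direction cannot be determined from the document. On the assumed shares, the effect is small if exits are few and equal: at most 1.0 point and six percentage points of power up to 10% per group. It can go either way if they are unequal. This should be changed because the remedy is cheap and unobserved outcomes cannot be restored later; no bias has been shown to have occurred. Confidence is medium, since the sponsor may have intended continued follow-up.

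**What to change.** In the dropout criteria:

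- Reword criterion (3) as study drug stopped by the investigator or attending physician, with date and reason recorded and the patient excluded from the per protocol analysis.
- State that patients under criteria (3), (4) and (5) remain on the existing visit schedule to day 30 for all outcomes.
- Limit the last-result rule to withdrawn consent and true loss to follow-up.

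Clinicians keep their discretion to reduce or stop study drug.

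Recruitment began on 1 September 2015 and was scheduled to run to 1 August 2018, so this needs a short amendment and a note to staff. The visit schedule already exists. After postoperative day 2 it means about 8 contacts per exited patient (4 daily on days 3 to 6, then about 4 weekly). If 5% of 864 exited (an assumption), that is 43.2 × 8 ≈ 346 contacts in all. For patients already exited, discharge date and vital status can be sought from hospital records where consent allows. If continued follow-up was always intended, one clarifying sentence does the same job.
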